### Study objectives

The main aims of the Cardiff arm of BRAINTRAIN are (1) to determine whether participants who receive rtfMRI NFT can down-regulate their brain activation while they are exposed to alcohol stimuli (or up-regulate their brain activation in response to pictures related to healthy goal pursuits), and (2) to determine whether, compared to control participants, the training helps patients to reduce their urges to drink and their consumption of alcohol and to bring about other improvements in their functioning. Additionally, secondary aims of the trial are to (1) identify participant characteristics that are related to success with the training, and (2) refine the parameters of the training in order to achieve an optimal intervention.

## Methods

### Ethical, safety, and privacy issues

The Wales Research Ethics Committee 1 approved the research protocol (Ref: 14/WA/1172). Additionally, the Research and Development Committee at Cwm Taf University Health Board, Cardiff and Vale University Health Board, and Aneurin Bevan University Health Board approved the protocol. Plans for modifying the trial protocol are unforeseen; however, should they arise, approval will be sought from the relevant ethics committees. Cardiff University as sponsor of the trial reserves the right to audit trial conduct should they have any concerns regarding conduct or safety. The South East Wales Trials Unit (SEWTU) is providing oversight of trial conduct. The protocol was designed in accordance with the SPIRIT (Standard Protocol Items: Recommendations for Interventional Trials) guidelines for interventional trials (Additional File 1).

A magnetic resonance imaging (MRI) safety-screening questionnaire is used to screen potential participants for MRI scanning. Patients who have contraindications for MRI scanning, such as metal implants in their bodies, are excluded. All information and data obtained from participants during the course of the study will be kept confidential by the research team in accordance with the UK Data Protection Act 1998.

### Design

The study is an unblinded, early-phase randomised feasibility trial that includes an experimental group and a control group of alcohol-dependent participants. The experimental group (*n* = 25) receive *f*MRI NFT in addition to treatment as usual (TAU). The control group (*n* = 25) receive only TAU. Randomisation is balanced for time since detoxification (more than 3 months, less than 6 months). The South East Wales Trials Unit is providing an online randomisation programme. A flowchart showing the sequence of recruitment, assessment, and intervention is shown in Fig. 1. A Standard Protocol Items: Recommendations for Interventional Trials (SPIRIT) diagram of the study period is shown in Table 1.

**Fig. 1 Fig1:**
[figure not shown]
Consolidated Standards of Reporting Trials (CONSORT) flow diagram of the phases of the BRAINTRAIN trial

**Table 1 Tab1:** Standard Protocol Items: Recommendations for Interventional Trials (SPIRIT) diagram

	Study period					
	Enrolment	Allocation				
Timepoint	Pre intervention	Time 0	Baseline	Post intervention	8-month follow-up	12-month follow-up
Enrolment:						
Eligibility screen	X					
Informed consent	X					
Allocation		X				
Interventions:						
rtfMRI NFT + TAU				X		
TAU				X		
Assessments:						
Alcohol Timeline Followback	X		X	X	X	X
Drinking Urges Questionnaire			X	X	X	X
Obsessive Compulsive Drinking Scale			X	X	X	X
Alcohol Stroop Test			X	X	X	X
Severity of Alcohol Dependence			X			
Thought Control Questionnaire			X			
Thought Control Ability Questionnaire			X			
Profile of Mood States			X		X	X
Hospital Anxiety and Depression Scale			X	X	X	X
Beck Depression Inventory			X	X	X	X

*rtfMRI* real-time functional magnetic resonance imaging, *TAU* treatment as usual

### Participant eligibility, recruitment, and screening

Eligible participants are alcohol-dependent patients who have successfully completed an inpatient detoxification programme 1 to 6 months before enrolment and are currently enrolled as outpatients. The programmes through which patients have been detoxified include those run by the Cwm Taf University Health Board, Cardiff and Vale University Health Board, and Aneurin Bevan University Health Board. Additional recruitment sites might be added at a later time. The TAU that patients receive includes psychological support, psychoeducation, and medical management of abstinence, for example with anticraving medication or disulfiram. Participants are randomly assigned to (1) a control group who continue to receive only TAU, or (2) an experimental group who receive rtfMRI NFT in addition to TAU.

Potential participants’ diagnosis of alcohol dependence (*International Classification of Diseases*, *tenth edition* (ICD-10): F102) is confirmed by inspection of their clinical records. Patients meeting this criterion are initially identified and approached to judge their interest in and suitability for participating in the study. These contacts are made either by (1) clinicians who are directly involved in the care of the patients, or (2) staff from the Health and Care Research Workforce in Wales.

Patients who are identified as suitable for the study are either invited personally by their primary clinician or they are sent a letter of invitation by their clinical team. Patients are also offered the opportunity to obtain more information about the study and to ask questions at informational events called *open days*, which are organised at the recruitment sites. During the open days, one or more members of the research team present details about the procedures and practicalities of the study (e.g. scanning procedures, questionnaires that are being used).

Once suitable patients have indicated an interest in participating in the study, they are invited to visit either one of the community alcohol and drug clinics or our research laboratory at Cardiff University. In either case, a research officer will give patients an information sheet about the study procedure, and will also ask participants to provide written informed consent to participate in the study (see Additional Files 2 and 3). If consent is obtained, participants are asked to complete several screening assessments as follows:The Mini International Neuropsychiatric Interview (MINI; [11]) is a short, structured interview for diagnosing psychiatric disorders based on *Diagnostic and Statistical Manual of Mental Disorders, fourth edition* (DSM-IV) and ICD criteria. Only the psychosis section of the MINI is administered. Patients identified as having a history of a psychotic disorder not related to alcohol dependence are excluded from participatingThe Wechsler Abbreviated Intelligence Scale (WASI-II; [12]) provides a global measure of patients’ level of intellectual functioning. Participants with an IQ below 70 are excluded because they would likely find the experimental tasks too difficult to completeAn in-house drug-use questionnaire measures participants’ use of illicit substances. Patients who have on-going regular use of illicit drugs, except for cannabis, are excludedThe Alcohol Timeline Followback (TLFB) Questionnaire [13] is used to determine whether patients have drunk alcohol since their discharge from their detoxification programme. Patients who have drunk any alcohol are excluded

Participants are informed that they are free to withdraw from the study at any time.

### Baseline assessment

During the baseline assessment, participants complete the following instruments: a demographic questionnaire (which asks about participants’ age, gender, level of education, and socioeconomic status); a National Health Service (NHS) resources utilisation questionnaire (which asks about the use of prescription medications and treatment services); and various standardised measures which are shown in Table 2. Patients are randomised after the baseline session.

**Table 2 Tab2:** Standardised measures administered

Measure	Description
Alcohol Timeline Followback (TLFB) Questionnaire [13]; primary outcome measure	Measures alcohol use during the 4 months immediately prior to patients’ entering treatment
Drinking Urges Questionnaire [22]; secondary outcome measure	Assesses participants’ desire to drink, expectations of positive effects following drinking, relief of withdrawal and negative affect following drinking, and intentions to drink
Obsessive Compulsive Drinking Scale (OCDS) [23]; secondary outcome measure	Measures respondents’ obsessive thoughts about alcohol use and compulsive behaviours related to drinking
Alcohol Stroop Test [24]; secondary outcome measure	Measures alcohol-related attentional distraction by alcohol-related stimuli
Severity of Alcohol Dependence Questionnaire [25]; primary outcome measure	Measures the degree to which patients are physically and psychologically dependent on alcohol
Thought Control Questionnaire (TCQ) [26]; BRAINTRAIN core outcome measure	Assesses the effectiveness of strategies used to control unpleasant or unwanted thoughts
Thought Control Ability Questionnaire (TCAQ) [27]; BRAINTRAIN core outcome measure	Measures individuals’ perceived ability to control unwanted and intrusive thoughts
Profile of Mood States (POMS) [28]; BRAINTRAIN core outcome measure	Measures anger, confusion, depression, fatigue, tension, and vigour
Hospital Anxiety and Depression Scale (HADS) [29]; BRAINTRAIN core outcome measure	Measure anxiety and depression
Beck Depression Inventory (BDI) [30]; BRAINTRAIN core outcome measure	Measures depression

### Assessment at NFT sessions

At each of the six NFT sessions across 4 months, patients in the experimental group complete the Drinking Urges Questionnaire (before and after the MRI scan), a self-rating of craving during the scanning session, the Alcohol TLFB (only after the last training session and covering the period from the baseline assessment to the present), the Alcohol Stroop Test (only after the last training session); the OCDS (only after the last training session); the HADS (only at the last training session); the BDI (only at the last training session); a debriefing interview questionnaire to identify strategies that participants used to down-regulate their brain reactions to alcohol stimuli (and up-regulate their brain responses to other goal-related pictures), their general experience with the procedure, and any adverse reactions that they might have experienced.

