### Four-month assessment of the control group

Four months after their baseline assessment, patients in the control group complete the Alcohol TLFB (covering the period from the baseline assessment to the present), the NHS resource utilisation questionnaire, the Drinking Urges Questionnaire, the Alcohol Stroop Test, the OCDS, and the POMS.

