### BRAINTRAIN core outcome measures

Some of the assessment instruments named above are part of the BRAINTRAIN core outcome measures, i.e. they are given in all five of the centres involved in the BRAINTRAIN project. Some of them (e.g. those measuring intellectual functioning and thought control) are used mainly to predict who will perform better at NFT and benefit more from it clinically. These measures will be used to stratify patients, and they are largely exploratory. Other instruments in this set measure nonspecific clinical factors and comorbidities (e.g. depression, anxiety) and are included across the different trials to increase the power of secondary outcome measures and to examine nonspecific effects of NFT on mental health (across different diagnoses and research protocols).

Participants are being sent reminders to attend the follow-up sessions.

Whenever possible, outcome data will be collected for all participants whether or not they adhere to the planned intervention. The data will be analysed according to the intention-to-treat principle.

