While in the scanner, participants in the experimental group are again exposed to alcohol-related stimuli, such as pictures of alcoholic drinks, and they are trained to regulate their responses in specific brain regions that are activated by the stimuli. In addition, participants are exposed to pictures showing alternative, socially desirable goals, such as family/relationships or employment. The rationale for including the two categories of stimuli is that we earlier demonstrated at a neural level that heavy drinking is associated with overvaluation of alcohol and undervaluation of alternative, socially desirable goals [14]. Moreover, consistent with motivational theory [15–17], it has been shown that problem drinkers’ success in reducing their drinking is associated with the degree to which they have other satisfying alternative goals to pursue and enjoy [16].

The size of the images that participants see corresponds to the level of activation. They are told to use any kind of mental strategy at their disposal (e.g. thinking about the negative consequences of drinking) that helps to reduce size of the image (in the case of alcohol pictures) or increase size of the image and thereby the degree of brain activation (in the case of healthy, goal-related pictures).

Experimental participants have six NFT training sessions spread across 4 months, and they are also asked to practice at home the mental strategies they used in the MRI scanner. They also (1) rate their urges to drink before, during, and after each training session, and (2) complete questionnaires and other tests to measure their alcohol consumption and other relevant aspects of their behaviour. Control participants complete the same measures that are timed to coincide with their administration to the experimental group. The primary outcome measures are obtained 4 months after the baseline assessment. Eight and 12 months after baseline assessment both groups complete a follow-up assessment battery.

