The behavioural data will be analysed using SPSS or another appropriate statistical software package. The primary analyses will compare the experimental and control groups on three drinking indices (percentage of days abstinent, drinks per drinking day, and percentage of days of heavy drinking) at the primary endpoint (4 months after the baseline assessment). For these analyses, a general linear model will be used. Covariates will include potential variables that determine participants’ success with the NFT (e.g. their age and gender and drinking indices at baseline) and the variables that were used to balance the two groups during randomisation. Effect sizes for the intervention will be evaluated using confidence intervals around the group difference. Analyses will be conducted separately for the follow-up assessments, again using general linear models adjusted for baseline covariates and randomisation variables. Outcome measures related to craving will be evaluated for both immediate and sustained effects of the NFT.

In exploratory analyses, data from the homework diaries will be examined for a potential relationship between the amount of self-regulation practice that participants report and their scores on craving and alcohol consumption. Finally, the relationship between nonalcohol-related measures (e.g. thought control ability, intellectual ability) and the alcohol-related outcome measures will be examined using analysis of covariance (ANCOVA) or correlational and regression analyses. Nonspecific effects of the NFT on participants’ mood will be examined using the measures related to emotional processes (e.g. the POMS).

A publication policy will be developed and reviewed during the course of the trial, which will include details of dissemination plans to health care professionals. Publications from the BRAINTRAIN consortium will be coordinated by the Executive Committee of BRAINTRAIN (chaired by the PI) in collaboration with the funding organisation. The trial results will be submitted for publication in an online open access journal.

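### The 4-month drinking, Stroop and OCDS assessments are tied to the last training session in the NFT arm but to the calendar in the control arm, and no 4-month visit is named for participants who stop training

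*Protocol article*

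**What the plan says.** For the NFT arm, the section Assessment at NFT sessions schedules "the Alcohol TLFB (only after the last training session and covering the period from the baseline assessment to the present". It ties the Alcohol Stroop and the OCDS to the same event, and gives the Drinking Urges Questionnaire before and after each scan.

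For the control arm, the only section headed as a four-month assessment reads "Four months after their baseline assessment, patients in the control group complete the Alcohol TLFB (covering the period from the baseline assessment to the present", followed by the urge questionnaire, Stroop and OCDS among others.

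Other statements set a common time point. The Intervention section says "The primary outcome measures are obtained 4 months after the baseline assessment" and "Control participants complete the same measures that are timed to coincide with their administration to the experimental group". The Analyses section places the three drinking indices "at the primary endpoint (4 months after the baseline assessment". On adherence, the section on core outcome measures says "Whenever possible, outcome data will be collected for all participants whether or not they adhere to the planned intervention".

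The Analyses section then specifies intention-to-treat on complete data, without imputation, with a check for bias in any missing cohort. Table 2 marks the TLFB as a primary outcome measure and the urge questionnaire, OCDS and Stroop as secondary.

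**The concern.** The trial compares the arms on drinking at one time point, but that time point is reached by different routes. In one arm the trigger is finishing the intervention; in the other it is the calendar. Three things are at stake.

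- **Window length.** Each TLFB runs from baseline to the day it is taken. If session six falls early or late, percentage of days abstinent and percentage of heavy drinking days are computed over a different span in the NFT arm than in controls.
- **Missingness.** Someone who stops NFT does not reach the event to which the TLFB is attached. If stopping NFT is related to drinking, a complete-data comparison can be distorted, and controls have no matching mechanism.
- **Measurement conditions.** Stroop and OCDS come after a scanning session in one arm only. For urges, two same-day readings exist in the NFT arm and the article does not say which is set against the control reading.

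**Working it through.** **1. The plan's own figure.** The Sample size estimation section states detectable effects of 0.8 (70% power) and 1.1 (90% power) with 20 per arm at the 0.05 level. A two-sample noncentral t calculation, taking the test as two-sided (the article does not say), gives 0.806 and 1.052, which round to the stated values. Fifty randomised less 20% leaves 40, also as stated. This point does not alter that calculation.

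**2. The schedules side by side.**

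| | NFT arm | Control arm |
|---|---|---|
| Trigger for TLFB, Stroop, OCDS | Last training session | Four months after baseline |
| TLFB window | Baseline to that visit | Baseline to that visit |
| Date fixed? | No: six sessions over 4 months, session six undated | Yes |
| Visit named if training stops | None | Not applicable |
| Scan at the same session | Yes | No |

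Table 1 does not settle the matter: its column is labelled post intervention, with no month. Nor do the two visits carry the same content. HADS and BDI appear in the NFT list but not in the control four-month list. POMS and the NHS resource questionnaire appear in the control list but not in the NFT one.

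**3. Window length (illustration only).** The documents give no relapse rate, post-relapse drinking rate or actual session dates. I assume no treatment effect, a constant relapse hazard, a proportion r relapsed by day 120, and drinking on a fraction q of days after relapse. Then:

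- λ = −ln(1 − r)/120
- expected share of a T-day window before relapse: p(T) = (1 − e^(−λT))/(λT)
- expected days abstinent = p(T) + (1 − p(T))(1 − q)

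Example, r = 0.5 and q = 0.5: λ = 0.693/120 = 0.00578. At T = 120, p = 0.5/0.693 = 0.721, so days abstinent = 0.721 + 0.279 × 0.5 = 86.1%.

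| r | q | 90 days | 120 days | 150 days |
|---|---|---|---|---|
| 0.3 | 0.5 | 93.9% | 92.1% | 90.3% |
| 0.5 | 0.5 | 89.0% | 86.1% | 83.4% |
| 0.5 | 1.0 | 78.0% | 72.1% | 66.9% |
| 0.7 | 1.0 | 65.9% | 58.1% | 51.7% |

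From the unrounded values, shortening the window by 30 days raises the figure by 1.8 to 7.7 points. Lengthening it by 30 days lowers it by 1.7 to 6.4 points. An early session six would flatter NFT and a late one would penalise it.

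**4. Loss of NFT stoppers.** The article gives no rate of stopping training, so no bias can be computed. The loss of precision can be shown. With 20 controls and a true effect of 0.8, power is 0.693 with 20 evaluable NFT participants, 0.669 with 18, 0.623 with 15 and 0.564 with 12. The larger worry is which participants are missing, and that cannot be sized from the documents.

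**The case against.** The best defence is that the article plans for the arms to coincide. Six sessions fill the same four months, control measures are timed to match, and the endpoint is fixed at four months for everyone. Outcome collection is promised regardless of adherence, and a check for bias in missing data is planned. The 8-month TLFB reaches back to the previous assessment, so a missed first period might be recovered then. A full protocol may also hold visit windows that the article leaves out.

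Much of this stands, and it rules out several stronger readings that a reader might infer:

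- **That the windows do differ.** The text shows only that they can. No session timings are given.
- **That NFT stoppers have no primary outcome planned.** The commitment to collect is explicit; what is lacking is a named visit.
- **That about 5 of 25 NFT participants would lack the outcome.** That figure is 20% of 25, the study dropout allowed for in both arms. It is not a rate of stopping NFT.
- **That missing data would favour NFT.** This needs stopping to be linked to relapse, which the documents do not establish.
- **That urges are measured only after alcohol-cue scanning.** A pre-scan reading exists, and a session may use goal pictures, so the last scan need not show alcohol.

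The defence does not remove the point. The statements of intent are general, while the arm-specific schedules are concrete and give different triggers. Following the NFT schedule as written yields a 4-month TLFB only after the last session. Recovery at 8 months is not described as a way to obtain the 4-month indices. A check for bias in missing data can reveal a problem but does not supply the missing observations.

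**Conclusion.** The point holds as an inconsistency between the stated endpoint and the NFT-arm schedule, with avoidable risk to the main between-group drinking comparison. Three elements are established from the text: different triggers for the TLFB, Stroop and OCDS; no named 4-month visit for NFT stoppers under a complete-data analysis; and Stroop and OCDS after a scanning session in one arm only. A fourth is an ambiguity: which urge reading is compared with controls.

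Neither the size nor the direction of any bias follows from the documents. The 2-to-8-point figure is an illustration. It rests on a constant hazard, 30% to 70% relapsed by day 120, drinking on 50% to 100% of later days, and a 30-day shift across the whole NFT arm. Smaller slippage would give smaller shifts.

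**What to change.** Reconcile the two assessment sections with the stated endpoint, as follows:

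- Hold the same 4-month assessment in both arms on a fixed date from baseline, whatever number of NFT sessions was attended, with the TLFB by telephone if needed.
- Derive the three drinking indices from the same calendar days in both arms.
- Give Stroop and OCDS before the scan or on a non-scan day.
- Name the pre-scan urge reading as the between-group measure and keep the post-scan reading for immediate effects.

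This concerns assessments only and leaves the training schedule untouched. The cost is a wording change plus a re-ordered visit or an additional call for some NFT participants. The article reports that recruitment was still under way, so the change could still serve participants who had not reached four months.
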